### Statistical analyses

Analysis of the primary outcome measure (number of logins to the site) will be conducted on an intention-to-treat basis (participants’ data is analysed in the group that they are randomised to, regardless of treatment they receive or the extent to which they engage with the intervention). Analysis of the secondary measures (psychological distress and subjective wellbeing) will also be conducted on an intention-to-treat basis. Missing data will be imputed using the Last Observation Carried Forward method. For the engagement measures where no previous data is available, missing data will be imputed using the group mean. To check the robustness of the primary findings, sensitivity analysis including a per-protocol analysis will be performed. Per-protocol is defined as three or more logins to the WorkGuru site. This baseline has been identified from average login data from the site and reflects login data from other studies (for a summary of login data for online health promotion interventions see [23]).

Primary and secondary hypotheses will be explored using predominantly descriptive statistics. The means and/or medians (as appropriate) will be reported with standard deviations. Ninety-five percent confidence intervals will be calculated. Standardised effect sizes will be calculated using Cohen’s *d* and, where appropriate, odds ratios will be reported. Exploratory inferential analysis will be performed using *t* tests, analyses of variance (ANOVAs) and correlations as appropriate. In recognition that this is a pilot study caution will be taken in interpreting and reporting these results.

Baseline differences between groups will be explored using the chi-square test and ANOVA (as appropriate) and, where possible, we will compare demographics of trial participants with the workforce of each organisation to see if trial participants are representative of the workforce.

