### Recruitment and randomisation

Six UK-based organisations will be approached to participate in this study. A sample size of 90 study participants will be recruited from the participating organisations. The sample size of 30 participants per arm is based on the optimum number of discussion group participants identified by WorkGuru, and is equal to the medium per arm sample size identified in an audit of sample sizes for pilot and feasibility studies [32]. Participants will be recruited through advertisements distributed via email, the organisations’ intranets and in-house magazines. All marketing information will include an email address inviting people who are interested in participating in the study to access information made available online or by emailing the first named author (SC). An information leaflet and a link to the online screening questionnaire, the short-form version of the Perceived Stress Scale (PSS-10; [33]) will be made available to all people who express an interest in the study. People who meet the inclusion criteria will automatically be sent a link to the online baseline questionnaire. The online questionnaires will be designed and distributed using Qualtrics survey software. Participants who complete the baseline questionnaire will be randomised. The first author will create an allocation schedule using a computer-generated randomisation sequence (random.org). An independent researcher not otherwise involved in the research will allocate each group (A, B or C) as an active condition (with or without a facilitated bulletin board) or as the WLC. Participants will be randomly allocated on a ratio of 1:1:1 to these groups. The study researchers will be blind to the group allocation.

Randomisation is being conducted at an individual level rather than at organisation or team level. This allows us to control for group stressors such as large-scale redundancies and team deadlines. One of the risks of individual-level randomisation is contamination between the groups (i.e. participants in the WLC talking with participants in an active intervention). The extent of contamination between the study groups will be monitored.

Participants using the bulletin board will be required to use a pseudonym to maintain researcher blindness. Individual-level randomisation has been chosen to control for group stressors (i.e. organisational, department or team change).

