### Inclusion and exclusion criteria

Inclusion criteria will be: age 18 years or over, employed by participating organisation, willingness to engage with an online CBT-based stress management intervention, access to a computer or tablet, access to the Internet, and a score of ≥20 on the PSS-10. No exclusion criteria have been set.

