The Goal Conflict Index (developed for this research) is a three-item questionnaire that asks participants to indicate on a five-point scale where 5 is ‘strongly agree’ the extent to which they agree with these statements:I often feel torn between my work and my home lifeI often have a number of competing duties that pull on my timeIt is often difficult to prioritise between the different goals in my life

Job autonomy is measured using the nine-item autonomy subscale of the more comprehensive 77-item Work Design Questionnaire [50]. The authors report good internal consistency for the autonomy subscale (*α* > 0.85).

To test whether the programme targets a pressing concern, we have included the question: ‘On a scale of 1–10 how important is it to you to reduce your level of workplace stress?’

As recommended by Rozental et al. [51], we have included a question to identify any possible negative effects of the intervention. Deterioration between pre and post treatment will be reported, and the self-report question: ‘What, if any, positive or negative effects caused by the programme/being in the control group did you experience?’ will be asked. Existing psychological illness will be monitored with the question: ‘Have you received a diagnosis of mental illness from your GP or a health care professional?’ Contamination between the groups will be monitored with the question: ‘During the course of this study to what extent have you discussed the research with colleagues who were allocated a different research group? (For example, if you are in the control group have you spoken with colleagues who are using the online programme?)’.

CAU (including medication for depression or anxiety) will be monitored using the Client Service Receipt Inventory ([52]; adapted for this study). The CSRI was developed to be easily adaptable to the context of the research in which it is being used [53].

Previous experience of stress management training will be monitored with the question: ‘Have you previously received stress management training including training on relaxation techniques and time management?’ To assess levels of sickness absence, participants will be asked if they had taken time off work for a stress-related complaint in the previous 8 weeks at time points 1, 2 and 3.

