Demographics will include: age, gender, fluency of written and spoken English, country of birth (UK, non-UK), relationship status, work role, number of working hours (low, middle, high), organisation, education level, income bracket and familiarity with online environment. The full list of measures is depicted in Table 3.

**Table 3 Tab3:** Measures

Measure (number of items)	T1	T2	T3
Primary measure: engagement			
Number of logins to the website		(X)	
Secondary measures: engagement			
Number of modules completed		(X)	
Number of pages visited		(X)	
Self-report engagement		(X)	
Secondary measures: effectiveness			
DASS-21 (21)	X	X	X
IWP Multi-affect Indicator (16)	X	X	X
Other measures			
Number of visits to discussion group		X^a^	
Number of contributions to discussion group		X^a^	
Existing psychological condition	X	X	X
Messages sent to and from coach		(X)	
Demographics	X		
Care as Usual (2)	X	X	X
Time Perception Index (5)	X	X	X
Goal conflicts (3)	X	X	X
Acceptability (6)	X	X	X
Credibility/expectancy (6)		2 weeks	
Level of importance (1)	X		
Negative effects of treatment (1)		X	X
Job autonomy (9)	X		
System Usability Scale (10)		(X)	
Client Satisfaction Questionnaire (8)		(X)	
Online Support Group Questionnaire (9)		X^a^	
Experience of stress management training (1)	X		
Sickness absence for stress-related complaint (1)	X	X	X
Contamination question (1)		X	X

T1 = baseline, T2 = 8 weeks (completion of intervention), T3 = 16 weeks (follow-up)

Groups: X = all three groups, (X) = MSG and discussion group, X^a^ = discussion group only

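### Last observation carried forward, the only stated missing-data method for DASS-21 and IWP, makes the estimated effectiveness depend on attrition in each arm

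*Protocol article*

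**What the plan says.** The Statistical analyses section sets two imputation rules. The general one is "Missing data will be imputed using the Last Observation Carried Forward method". The other covers usage data: "For the engagement measures where no previous data is available, missing data will be imputed using the group mean". DASS-21 and IWP are collected at baseline (T1), 8 weeks (T2) and 16 weeks (T3) according to Table 3, so they have earlier values and fall under the first rule. The same section says of them: "Analysis of the secondary measures (psychological distress and subjective wellbeing) will also be conducted on an intention-to-treat basis".

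Under Recruitment and randomisation, "Participants who complete the baseline questionnaire will be randomised", so every randomised participant has a baseline score to carry forward. Entry requires "a score of ≥20 on the PSS-10" (Inclusion and exclusion criteria).

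The results feed two stated purposes. The Abstract wants an estimate of potential effectiveness, and Aim of the study lists an effect-size prediction among the objectives. "Standardised effect sizes will be calculated using" Cohen's *d*. Separately, Other measures promises that "Deterioration between pre and post treatment will be reported", without saying whether imputed scores enter that report.

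The only sensitivity analysis named is per-protocol, defined as three or more logins and attached to the primary (login) findings.

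**The concern.** With three assessments, carrying forward does one of two things. A participant lost before T2 receives the baseline score at T2 and T3, which is zero change. A participant lost after T2 keeps the T2 score at T3. Neither value is an estimate of where that person would have been, and once filled in it is treated as a measurement, so the intervals do not reflect the uncertainty.

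The rule does no harm to the mean if scores do not move in any arm and dropout is random. That is doubtful here. Participants are selected for high perceived stress, so some downward drift is plausible in all arms, wait list included, and the intervention is meant to lower distress. The protocol's Background and Discussion describe attrition as a serious and unquantified problem in workplace settings. The arms also receive different levels of support, so unequal dropout is plausible.

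What is at stake is the effectiveness estimate, particularly against wait list, which the Discussion says was included to show the effect compared with no treatment. Equal dropout shrinks a real effect. Unequal dropout can shrink it, inflate it or create one. The deterioration report could be affected as well, depending on which scores it uses.

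**Working it through.** **Figures in the plan.** The protocol gives no attrition rate, no expected change on DASS-21 or IWP, and no figure for the effect of imputation, so there is no stated result to reproduce. The sample size is 3 × 30 = 90. The entry cut-off is about one SD above the cited population mean: 13.02 + 6.35 = 19.37, against the cut-off of 20.

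**Formula.** Let *a* and *c* be the mean improvements to T2 in the active and wait-list arms, in SD units, and pA and pC the proportions lost before T2, at random. Those lost contribute zero change, so

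- true difference = a − c
- expected difference under carrying forward = (1 − pA)·a − (1 − pC)·c

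**A real effect.** Assume a = 0.70 and c = 0.30, so the true difference is 0.40.

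| Dropout, active/wait list | Calculation | Result |
|---|---|---|
| 20%/20% | 0.8 × 0.70 − 0.8 × 0.30 | 0.32 |
| 40%/20% | 0.6 × 0.70 − 0.8 × 0.30 | 0.18 |
| 20%/40% | 0.8 × 0.70 − 0.6 × 0.30 | 0.38 |
| 10%/40% | 0.9 × 0.70 − 0.6 × 0.30 | 0.45 |

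**A smaller effect.** With a = 0.50 and c = 0.20 (true 0.30), the results are 0.24 at 20%/20%, 0.18 at 40%/40%, 0.12 at 40%/10% and 0.33 at 10%/40%.

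**No effect.** With a = c = 0.30, equal dropout gives 0.00. Dropout of 40%/10% gives 0.6 × 0.30 − 0.9 × 0.30 = −0.09, and 10%/40% gives +0.09. Unequal attrition alone produces an apparent difference.

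**Check by simulation.** With 200,000 per arm, an assumed pre-post correlation of 0.6, improvements of 0.50 and 0.20, and random 40%/10% dropout, carrying forward gave *d* = 0.12 and observed data gave 0.30, against a true value of about 0.30. When those who worsened were more likely to drop out (same 40%/10%), carrying forward gave 0.22 and observed data 0.41, against the same true value.

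**Consequence if used for sizing.** At 80% power and two-sided 5%, n per arm = 2 × (1.96 + 0.8416)² / d² = 15.70 / d².

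- d = 0.40: 98.1, so 99 per arm
- d = 0.18: 484.5, so 485 per arm
- d = 0.45: 77.5, so 78 per arm

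**Deterioration, if imputed scores are used.** Anyone lost before T2 has a change of exactly zero. In the simulation, with deterioration taken as a rise of more than 0.5 SD and random 40%/10% dropout, a true rate of 13.2% in the active arm appeared as 7.9%, and 21.7% in the control arm as 19.6%. When those who worsened dropped out more, 13.1% appeared as 3.6% and 21.7% as 16.9%.

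**The case against.** The strongest reply concerns weight. DASS-21 and IWP are secondary. The primary outcome, logins, has no earlier value and is not subject to this rule. The analysis is mainly descriptive, inferential tests are exploratory, and the protocol calls the pilot underpowered and promises cautious interpretation. With 30 per arm, the standard error of *d* is about √(2/30) = 0.26, so its 95% interval is roughly ±0.51 even without dropout. Biases of 0.02 to 0.22, as in the 0.40 example, lie well inside that. All of this stands, and it lowers the severity. It does not justify adding an avoidable bias to an estimate the study sets out to provide.

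Selection is on the PSS-10 while the outcomes are other scales, so the amount of drift is unknown. That also stands, and it is why the changes above are assumptions. Nor is carrying forward always the worst choice: in the non-random dropout scenario it came closer to the truth than observed data alone. This argues against simple complete-case analysis and for a sensitivity analysis. It was not a test of the model or the multiple imputation proposed below.

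Some safeguards exist. Attrition is an objective, reporting follows CONSORT, the wording leaves room for further sensitivity analyses, and an open question on positive or negative effects goes to all three groups at T2 and T3. These help, but none of them varies the missing-data assumption, and the open question reaches only those who respond.

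**Conclusion.** The concern holds as a point that should be fixed. The protocol itself fixes carrying forward as the sole stated method for DASS-21 and IWP, and no named sensitivity analysis tests it. If mean scores change over time, the effect size varies with attrition by arm. A true 0.40 SD becomes anything from 0.18 to 0.45 across the dropout patterns shown. Those figures rest on assumed improvements and on random loss before T2. They show how the bias works and do not predict its size in this trial.

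Four stronger readings might be inferred and are not supported:

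- **That every dropout is scored as unchanged.** This is true only of loss before T2. After T2, any change already recorded is kept.
- **That the definitive trial will be mis-sized.** Aim of the study names no outcome for its effect-size prediction, and the Discussion's worked example is an adherence measure. The move from 99 to 485 per arm applies only if the next trial is sized on this estimate.
- **That deterioration will be hidden.** This follows only if imputed scores are used, and the protocol does not say.
- **That the trial's main result is compromised.** The primary outcome is outside this rule.

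**What to change.** For DASS-21 and IWP, replace carrying forward with one of:

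- a likelihood-based repeated-measures model for T2 and T3, with arm, time, arm-by-time interaction and the T1 score as covariate, fitted to all observed data; or
- multiple imputation using baseline variables and, in the two active arms only, logins (the wait list has no access until 16 weeks).

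Both assume that dropout is explained by the observed data, so add a delta-adjusted sensitivity analysis in which missing outcomes are made progressively worse, separately by arm.

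State that deterioration is reported on observed T2 scores, with bounds that count all missing participants first as not deteriorated and then as deteriorated.

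The cost is a change of wording, slightly more analysis work and wider confidence intervals. No additional data are needed.

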### Intervention

The online CBT-based stress management intervention WorkGuru is presented on a secure platform that participants log on to using email addresses and a self-generated password. WorkGuru is a modular intervention that is based on the psychological principles of CBT, positive psychology, mindfulness and problem solving. It has been designed to increase self-awareness, improve flexible thinking and teach active coping skills. There are 10 modules that individuals can select to complete (see Table 2 for more information). Seven of those modules comprise the core modules, which all participants will be advised to complete. The modules consist of a combination of educational reading and audio, short animations, and interactive exercises. Participants can complete a questionnaire and receive suggestions for modules that they may find useful, or they can chose the modules themselves. As well as the modules, participants can complete eight self-monitoring standardised questionnaires, for example: the Perceived Stress Scale [33], the Subjective Happiness Scale [34] and the Brief Resilience Scale [35]. Participants have the option to opt in to a weekly email (the Monday Morning Message) that will reinforce messages of positive thinking and healthy working practices. They can also set themselves email reminders to visit the site. To encourage engagement, the coach will contact each participant through the site three times during the course of the 8-week programme (when an account is created, at 2 weeks and at 6 weeks). Participants can chose to share their work with the coach, and to contact the coach at anytime through the site to ask for feedback or additional help or advice. The coach will respond within 24 h. The coach has a postgraduate-level qualification in executive coaching.

**Table 2 Tab2:** WorkGuru modules

	Module title	Module content	Suggested completion time
1.	Learn about me and my values^a^	Two questionnaires designed to help identify and prioritise work and life values. Exercise to prioritise those values	70 min
2.	Identify the things that cause me stress^a^	Psychoeducational information on stress, a Stress Diary and an exercise designed to help individuals analyse their stress diaries looking for patterns to their stress trigger, and the helpful and not so helpful ways they respond to stress	90 min (plus Stress Diary)

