#### Primary and secondary outcome measures

The primary outcome measure of the study is engagement (the number of logins to the site); the secondary outcome measures include further engagement measures (the number of pages visited, the number of modules completed, and self-report engagement) and measures of effectiveness (the English language short-form version of the Depression, Anxiety, Stress Scale (DASS-21; [38]) and the wellbeing at work indicator (IWP Multi-affect Indicator; [39])). The DASS-21 has been designed to measure the negative emotional states of depression, anxiety and stress. In a review of the scale Henry and Crawford [40] reported a Cronbach’s alpha of .93. The scale was described as moderately sensitive to change in a clinical sample of depressed subjects [41]. The IWP Multi-affect Indicator is a 16-item measure of subjective wellbeing at work. Alpha coefficients for this scale range from .75 to .90 [42].

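### Group-mean imputation of missing engagement measures, logins included, shrinks the SD and makes the confidence interval too narrow whenever it is used

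*Protocol article*

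**What the plan says.** The Statistical analyses section uses Last Observation Carried Forward for missing data in general and then adds: "For the engagement measures where no previous data is available, missing data will be imputed using the group mean".

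The rule reaches the primary outcome. Under Primary and secondary outcome measures: "The primary outcome measure of the study is engagement (the number of logins to the site". Table 3 marks logins, modules, pages and "Self-report engagement" at T2 only, in the two active arms (the table note reads "Groups: X = all three groups, (X) = MSG and discussion group"). With no earlier value to carry forward, the group mean is what remains.

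The analysis is by intention to treat, with participants kept in their arm "regardless of treatment they receive or the extent to which they engage with the intervention". The results are to be reported as means or medians with SDs, 95% confidence intervals and Cohen's d, with exploratory t tests and ANOVA. Supplying an effect size for the definitive trial is a listed objective under Aim of the study. The one sensitivity analysis named is per-protocol, at three or more logins.

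**The concern.** Filling gaps with the arm mean treats unknown values as known and places them exactly at the centre. The arm mean stays at the observed-case mean, while the SD shrinks and the sample looks larger than it is. These are the quantities the pilot is meant to hand on: an SD that is too small, or a d that is too large, would undersize the definitive trial.

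A second issue depends on how non-use is recorded. On the platform "participants log on to using email addresses and a self-generated password" (Intervention), and the coach's first contact is tied to account creation. A randomised person who never registers may therefore leave no platform record, although that person's engagement is in truth zero. The document does not say whether such a person is scored 0 or treated as missing. If missing, the rule credits them with their arm's average.

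**Working it through.** **Inputs.** The arm size is 30 ("The sample size of 30 participants per arm is based on the optimum number of discussion group participants identified by WorkGuru"). For allocation: "Participants will be randomly allocated on a ratio of 1:1:1 to these groups". So 3 × 30 = 90, which reproduces the stated total. No figure in the protocol depends on the imputation rule. The Discussion cites d = 0.53 from a study of adherence before and after delivery changes; 2 × 8.8 / √1106 = 0.529 agrees. It serves below only as an illustration. No missing rate is given, so 10 to 50% per arm is **assumed**.

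**Step 1: SD and d.** With k of n values observed and the rest set to the observed mean, the sum of squares is unchanged, but the divisor becomes n − 1 instead of k − 1.

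- SD ratio = √((k − 1)/(n − 1)). At 30% imputed, k = 21 and √(20/29) = 0.83.
- For a given mean difference, d is multiplied by the inverse: 1/0.83 = 1.20.

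This holds whatever the reason for missingness.

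**Step 2: interval width and coverage.** The rule's half-width for a difference in means is t(58) × SD ratio × √(2/30). The observed-case half-width is t(2k − 2) × √(2/k). At k = 21, the rule's half-width divided by the true standard error is 2.00 × 0.830 × √(21/30) = 1.39. The correct multiplier is 2.02, so the width ratio is 0.69. Coverage is 2F(1.39) − 1 on 40 degrees of freedom = 82.8%. Coverage assumes values missing completely at random.

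| Imputed | k | SD × | d × | 0.53 becomes | CI width × | Coverage |
|---|---|---|---|---|---|---|
| 10% | 27 | 0.95 | 1.06 | 0.56 | 0.90 | 92.2% |
| 20% | 24 | 0.89 | 1.12 | 0.60 | 0.79 | 88.2% |
| 30% | 21 | 0.83 | 1.20 | 0.64 | 0.69 | 82.8% |
| 40% | 18 | 0.77 | 1.31 | 0.69 | 0.58 | 75.7% |
| 50% | 15 | 0.70 | 1.44 | 0.76 | 0.48 | 66.6% |

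A simulation at 30% missing at random (8,000 runs; negative-binomial logins with assumed mean 4 and dispersion 1.5) gave an SD of 3.12 against 3.78, and 82% coverage.

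**Step 3: consequence for sizing.** Required sample size varies as 1/d², so it is multiplied by (k − 1)/(n − 1). This is 23/29 = 0.79, 20/29 = 0.69 and 17/29 = 0.59 at 20, 30 and 40% imputed.

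**Step 4: only if people with no record count as missing.** Assume users average 4 logins in both arms.

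- 30% never-users in each arm: the true mean is 0.7 × 4 = 2.8; the rule reports 4.0.
- 40% against 20% never-users: the true means are 0.6 × 4 = 2.4 and 0.8 × 4 = 3.2, a difference of 0.8 (d about 0.23). The rule reports 4.0 and 4.0, so the difference vanishes. Simulated coverage of the true difference was 72%.
- If instead non-use is equal at 30% and user means differ by Δ, the true difference is 0.7Δ but the rule reports Δ, which is 1/0.7 = 1.43 times too large.

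The error in the arm comparison can therefore go either way.

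**The case against.** The strongest reply is that logins, pages and modules are system counts, and the Discussion itself notes that use of an internet intervention can be measured objectively. On that reading a non-user is an observed 0, and the rule touches only values that are really absent, chiefly self-report engagement, a secondary outcome. This largely stands. A reader might infer from the rule that non-users are given their arm's average, but no sentence says so. An account holder who never logs in would normally be a recorded 0; the doubt concerns mainly people who never open an account.

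It also stands that the missing rates and the never-user splits above are assumptions, and that the equal user means were chosen so that the cancellation is exact. Nor can the two mechanisms be added together: a reader might conclude that the rule both erases the arm difference and inflates d, but in the cancelling example d goes to about zero.

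Finally, the study is a self-declared underpowered pilot with mainly descriptive analysis. Inflated test size therefore matters little, as there is no confirmatory test. That caution does not repair an SD, interval or d passed on to the next trial. Further sensitivity analyses may sit in an analysis plan not shown, but the one named selects on logins and does not test the imputation.

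**Conclusion.** The point holds in limited form. The protocol fixes a rule that gives too small an SD and too narrow an interval every time it is applied; it covers the primary outcome, and nothing else in the document corrects it. With 20 to 40% imputed, an assumed range, the SD is about 0.89 to 0.77 of its value, d for a given mean difference is about 12 to 30% too large, and coverage is about 88 to 76%. With few values imputed the damage is small.

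The bias from non-users is conditional. If people without an account are treated as missing, mean engagement is overstated and a between-arm difference in non-use can be hidden or distorted, with unknown direction for d. If all non-users are coded 0, logins are largely unaffected and the problem rests mainly on self-report engagement, which is collected only at T2 and could well be missing more often among people who disengaged. The document does not settle which case applies.

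**What to change.** Replace the group-mean sentence with two rules.

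- **Logins, pages and modules:** take them from the platform for every randomised participant in the two active arms. Score confirmed non-use, including no account created, as 0. Leave a true linkage or technical failure missing and report how many there are; absence of a record alone should not be scored 0 without that check.
- **Self-report engagement:** drop mean imputation. Use multiple imputation that includes the platform measures and baseline variables, with the observed-case result alongside. With about 30 per arm, observed-case reporting alone would also be acceptable.

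The cost is analysis wording only, with no new data or participants. Mean engagement will look lower and the intervals wider.
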